## Background

Humeral shaft fractures are associated with a profound temporary (in elderly sometimes even permanent) impairment of independence and quality of life. Fractures of the humeral shaft account for 1-3% of all fractures [1]. The cumulative incidence shows a peak in the working population (14.5/100,000 person years) as well as in the elderly (60/100,000) [1-3].

Humeral shaft fractures can be treated operatively or non-operatively. Operative treatment is mostly performed by intramedullary nailing, plate osteosynthesis, or external fixation. Non-operative immobilization is mostly done with a functional (Sarmiento) brace [4]. Operative and non-operative treatment strategies both have their pros and cons. Operative fracture fixation allows for early mobilization, which may lead to earlier functional recovery and reduced pain. However, surgical complications and fixation failure may occur [5]. Non-operative treatment may be associated with more pain (as the fracture is not stabilized) and discomfort (due to pain and immobilization) in the first weeks and may be associated with a higher malunion risk due to the lack of fracture re-alignment [6,7]. Longer immobilization may delay functional recovery.

Complications of operative and non-operative treatment overlap and data are lacking to determine treatment relatedness. Non-union occurs in 15-30% after operative treatment [5] versus 2-23% after non-operative treatment (for which most patients require secondary surgical treatment) [6,7]. The most feared disabling complication is radial nerve palsy, occurring in 2-17% of all patients [8-10]. A systematic review (n = 4,517 patients) reported an average radial nerve palsy of 11.8%. Although 70% recover spontaneously, the palsy was permanent in 12% of cases accounting for a substantial impairment and costs [9].

Regaining function is extremely important from a patient and societal perspective. From the few retrospective and prospective case series published, each using other outcomes, better functional outcome is expected after operative treatment [8,11-17].

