The best type of treatment is still debated. Surgeons state that their experience, patient characteristics and expected physical demands in daily living guides treatment decision. In the elderly patients, some surgeons might prefer immobilization while others may primarily operate as they fear inferior functional outcome after non-operative treatment. In younger patients, some surgeons directly perform a surgical intervention while others primarily choose non-operative immobilization, followed by surgical intervention if needed. However, our retrospective study showed an approximately 50% operation rate irrespective of fracture subclass with no obvious differences in patient or fracture characteristics across classes [18]. Since randomized or high-quality comparative observational studies are lacking, a recent Cochrane review concluded there is no evidence of sufficient scientific quality available to inform the decision to operate or not [19]. High-quality clinical studies are thus urgently needed to resolve this clinically relevant problem. RCTs for this injury have shown feasibility issues; one RCT continued as an observational study due to severe recruitment problems [20]. The HUMMER study is designed to provide the best achievable evidence to answer this unresolved problem using an observational trial design.

The primary objective of this study is to examine the effect of operative versus non-operative treatment on the DASH (Disabilities of the Arm, Shoulder, and Hand) score, reflecting functional outcome and pain of the upper extremity, in adult patients who sustained a humeral shaft fracture. Secondary aims are to examine the effect of operative versus non-operative treatment on functional outcome, the level of pain, range of motion of the shoulder and elbow joint, the rate of secondary interventions and complications, the time to resumption of work and activities of daily living, health-related quality of life, costs, and cost-effectiveness in these patients.

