### Study population

All persons aged 18 years or older presenting to the ED with a humeral shaft fracture (AO type 12A or 12B) are eligible for inclusion [33]. The AO type 12C fractures will be excluded due to their low occurrence rate. Humeral shaft fractures are defined as fractures located in the area between the surgical neck and the area immediately above the supracondylar ridge.

Patients meeting the following inclusion criteria are eligible for enrolment:

1. Adult men or women aged 18 years or older (with no upper age limit)

2. A fracture of the humeral shaft, AO class 12A or 12B (confirmed on X-ray)

3. Operation within 14 days after presentation to the ED (if this is the treatment of choice)

4. Provision of informed consent by patient

If any of the following criteria applies, patients will be excluded:

1. Patients with concomitant injuries affecting treatment and rehabilitation of the affected arm

2. Patients with a humeral fracture treated with an external fixator

3. Patients with a pathological, recurrent or open humeral shaft fracture

4. Patients with neurovascular injuries requiring immediate surgery (excl. radial nerve palsy)

5. Additional traumatic injuries of the affected arm that influence upper extremity function

6. Patients with an impaired upper extremity function (*i.e.*, stiff or painful arm or neurological disorder of the upper limb) prior to the injury

7. Retained hardware around the affected humerus

8. Patients with rheumatoid arthritis

9. Bone disorder which may impair bone healing (excluding osteoporosis)

10. Patients incapable of ensuring follow-up (*e.g.*, no fixed address or cognitive impairment)

11. Insufficient comprehension of the Dutch language to understand the rehabilitation program and other treatment information, as judged by the treating physician of researcher

Exclusion of a patient because of enrolment in another ongoing drug or surgical intervention trial will be left to the discretion of the attending surgeon on a case-by-case basis.

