The range of motion (ROM) of the shoulder (*i.e.*, abduction and forward flexion) and the elbow joint (*i.e.*, flexion and extension) will be measured using a goniometer. Both sides will be assessed separately, and the loss of ROM will be calculated.

Complications will be recorded from medical charts. Complications may include: 1) surgical site infection; 2) wound dehiscence; 3) skin problems (*e.g.*, skin at risk, skin necrosis); 4) dystrophia; 5) radial nerve palsy; 6) malunion; 7) implant failure (screw breakout); 8) cuff pathology; 9) secondary fracture dislocation; or 10) non-union. Non-union is defined as a failure to heal at twenty-six weeks post fracture with no progress towards healing seen on the most recent radiographs [37].

Secondary intervention within one year of initial treatment to promote fracture healing, relieve pain, treat infection, or improve function will be recorded from medical charts. Interventions will be categorized as: 1) osteosynthesis with or without bone grafting; 2) implant exchange with or without bone grafting; 3) implant removal; 4) incision and drainage for superficial surgical site infection; or 5) incision and drainage for deep surgical site infection. The indication and admission duration for all intervention will also be recorded.

Presence of radiographic healing will be determined using X-rays. Fracture consolidation is defined when one of the three criteria listed is present; 1) bridging of fracture by callus/bone trabeculae or osseous bone; 2) obliteration of fracture line/cortical continuity; or 3) bridging of fracture at three out of four cortices.

The time to resumption of work and activities of daily living will be recorded using a custom-made questionnaire.

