### Statistical analysis

Data will be analyzed using the Statistical Package for the Social Sciences (SPSS) version 21 or higher (SPSS, Chicago, Ill., USA) and will be reported following the STrengthening the Reporting of OBservational studies in Epidemiology (STROBE) guidelines. Normality of continuous data will be assessed by inspecting the frequency distributions (histograms), and homogeneity of variances will be tested using the Levene’s test.

Descriptive analysis will be performed to report baseline characteristics (intrinsic variables and injury-related variables) and outcome measures for both treatment groups.

For continuous data mean and SD (parametric data) or medians and percentiles (non-parametric data) will be calculated and reported. For categorical data, numbers and frequencies will be calculated and reported for both treatment groups.

Univariate analysis will be performed in order to test the difference in the primary and secondary outcome measures between the operative and the non-operative group. Continuous data such as the DASH score at the different time points (primary outcome) will be tested using a Student’s T-test (parametric data) or a Mann Whitney U-test (non-parametric data). Chi-square analysis will be used for statistical testing of categorical data such as the nonunion rate. A p-value <0.05 will be taken as threshold of statistical significance.

For the primary analysis, a mixed linear regression model will be developed in order to model the relation between different covariates and the DASH score over time. Intrinsic and fracture-related variables that display a p-value <0.5 in univariate analyses will be added as covariate. Similar models will be developed for the Constant, SF-36, and EQ-5D score. Subgroup analysis (*e.g.*, elderly versus <65 years) will be performed.

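### The non-union definition looks only at week 26, so fractures operated on earlier for failed healing can leave the non-union count in either group

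*Protocol article*

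**What the plan says.** Under Outcome measures, non-union is one of ten listed complications and has a fixed definition: "Non-union is defined as a failure to heal at twenty-six weeks post fracture with no progress towards healing seen on the most recent radiographs". Study procedures ties the assessment to the six-month radiograph and says that this visit should not be brought forward. Under Statistical analysis the rate is compared between treatment groups: "Chi-square analysis will be used for statistical testing of categorical data such as the nonunion rate".

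Surgery after the initial treatment is recorded separately. Outcome measures states: "Secondary intervention within one year of initial treatment to promote fracture healing, relieve pain, treat infection, or improve function will be recorded from medical charts". The categories include osteosynthesis and implant exchange. On the reason for surgery it adds: "The indication and admission duration for all intervention will also be recorded". The rate of secondary interventions is a secondary outcome in its own right.

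Study population limits an initial operation to 14 days after presentation, so later fixation after a non-operative start is not initial treatment. The Background says of younger patients that some surgeons operate directly while "others primarily choose non-operative immobilization, followed by surgical intervention if needed".

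The article does not say how to classify a patient operated on for failed healing before week 26.

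**The concern.** The non-union rate is meant to show how often the initial treatment fails to produce union. The definition instead reads the state of the fracture at one date, whatever has been done to it by then. For a patient re-operated on at, say, week 16, the most recent films show the fracture after the second procedure. If they show healing or progress, the patient does not meet the definition.

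The more readily failed healing is dealt with early, the lower the counted rate. If that readiness differs between groups, the chi-square test compares a mixture of healing and re-operation practice. A group could show a low non-union rate partly because its failures had already been operated on. Listing those operations in a separate table does not change the rate that is tested.

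**Working it through.** **The plan's own figures.** The article gives no sample size, power or expected count for non-union. Its only calculated figure is for DASH: means 16 and 10, SDs 16 and 10, two-sided 5%, 80% power. With average variance (16² + 10²)/2 = 178, n = 2 × (1.960 + 0.842)² × 178 / 6² = 77.6, so 78 per group, as stated. This has no bearing on non-union.

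**Who leaves the count.** Take a fracture that is failing to heal under the initial treatment:

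| Course | Non-union by the definition? |
|---|---|
| No intervention before week 26; unhealed, no progress | Yes |
| Intervention before week 26; still unhealed, no progress at week 26 | Yes |
| Intervention before week 26; healed or progressing at week 26 | No |

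Only the third row is lost. It can occur after conversion of a non-operative patient to osteosynthesis, or after early implant exchange in an operated patient.

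**Is there time for it?** Under Intervention, usual non-operative care is 1–2 weeks of initial immobilization and then 4–6 weeks in a brace, that is 5–8 weeks in all. This leaves 26 − 8 = 18 to 26 − 5 = 21 weeks before the assessment. It shows only that early conversion is possible, not how often it happens.

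**Size, as illustration.** Let p be the rate of failed healing under the initial treatment and f the share of these patients who are operated on before week 26 and are healed or progressing by then. The counted rate is p × (1 − f). The Background gives non-union of 2–23% after non-operative and 15–30% after operative treatment. The documents do not give f; 25% and 50% are assumptions.

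- p = 15%: 0.15 × 0.75 = 11.3%; 0.15 × 0.50 = 7.5%.
- p = 23%: 0.23 × 0.75 = 17.3%; 0.23 × 0.50 = 11.5%.
- p = 2%: 0.02 × 0.75 = 1.5%; 0.02 × 0.50 = 1.0%.

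**Effect on the comparison.** Take the planned 200 per group, ignoring losses.

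- Equal p = 15%, f = 50% in both groups: 7.5% versus 7.5%. Both rates are understated, but no difference is created.
- Equal p = 15%, f = 50% in one group and 0 in the other: 15 versus 30 events. Chi-square = 400 × (30 × 185 − 15 × 170)² / (200 × 200 × 45 × 355) = 5.63, p = 0.018 without continuity correction. The definition alone would produce this difference.
- p = 23% non-operative and 15% operative, with f = 0 in the operative group: the difference (non-operative minus operative) is 23 − 15 = +8.0 points at non-operative f = 0, 17.25 − 15 = +2.3 at f = 25%, and 11.5 − 15 = −3.5 at f = 50%.

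The bias in the comparison therefore depends on the difference in f between groups, about which the article says nothing.

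**The case against.** **A fixed radiographic time point is defensible.** Before week 26 a fracture is by definition not yet a non-union, and whether an early-converted fracture would have united cannot be observed. Treatment is unblinded and left to the surgeon, so counting early surgery lets the surgeon's threshold enter the outcome. This stands, and is why the components should be reported separately with the 26-week definition beside them. It does not rescue the 26-week rate as the only one: the surgeon's threshold already affects that rate, by removing cases.

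**The events are captured elsewhere.** Secondary interventions are an outcome, with the indication recorded. This makes repair possible, but the tested non-union rate is unchanged.

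**Combining the two could be left to a fuller document.** That would hold if the article were silent. It states the definition, the assessment time and the test, and the objection is to that stated rule.

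**Stronger readings that the documents do not support.** A reader might infer that every converted patient drops out; one who is still unhealed without progress at week 26 still counts. A reader might infer that converted patients are counted as united; consolidation has its own radiographic criteria, and not being a non-union is not the same as having healed. A reader might infer that the loss falls mainly on the non-operative group; the remark about later surgery is Background on surgeons' habits, with no timing, frequency or link to failed healing. Early operative revisions are lost in the same way, and the Background gives the operative group the higher non-union range.

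**Conclusion.** The point holds in a limited form. As written, the definition omits patients in either group who had an early intervention for delayed or failed healing and are healed or progressing by week 26. The counted rate is then below the rate at which the initial treatment failed, by the proportion f. The between-group comparison is biased if f differs between groups. A difference is plausible, but its existence, direction and size cannot be established from the article.

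The figures show what could happen and are not estimates. The contrast of 15% versus 7.5% and the change of sign at 23% versus 15% both need f = 50% in one group, none in the other. It should not be concluded that the planned comparison will mask or reverse a true difference.

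The consequence is confined to one component of a secondary outcome. The primary DASH outcome, its model and the sample size are unaffected.

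**What to change.** In both groups, analyse failure of union of the initial treatment, defined as either (a) non-union at 26 weeks as now written, or (b) an earlier secondary intervention whose recorded indication is delayed or failed healing. Report (a) and (b) separately by group, and give the comparison on the 26-week definition alone as a sensitivity analysis. State the rule before the data are analysed.

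The cost is small. Secondary interventions and their indications are already collected. The intervention date is not listed as a data item and is only implied by the one-year limit, so it must be taken from the charts. The downside is that (b) will include some fractures that would have healed without the intervention; separate reporting shows how much of the result rests on them. The change concerns classification and analysis only and leaves whether or when to operate untouched.

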### Outcome measures

The Disabilities of the Arm, Shoulder and Hand (DASH) outcome measure will serve as primary outcome measure. The DASH is a validated 30-item, self-report questionnaire designed to help describe the disability experienced by people with upper-limb disorders and also to monitor changes in symptoms and function over time [34,35]. It is scored in two components: the disability/symptom section (30 items, scored 1–5) and two optional Work and high performance Sport/Music modules (each 4 items, scored 1–5). The DASH disability/symptom score is a summation of the responses to 30 questions on a scale of 1 to 5, with an overall score ranging from 0 (no disability) to 100 (severe disability). At least 27 of the 30 items must be completed for a score to be calculated. The DASH optional modules aim to measure symptoms and function in athletes, performing artists and other workers whose jobs require a high degree of physical performance. These optional models are scored separately and each contains four items, scored 1–5. All items must be completed for a score to be calculated.

The secondary outcome measures are:

• Constant score

• Pain level at both sides (VAS)

• Range of Motion of the shoulder and elbow joint at both sides

• Rate of complications

• Rate of secondary interventions

• Time to resumption of work and other activities of daily living

• Health-related quality of life: SF-36 and EQ-5D

• Radiographic healing

• Cost of health care use and production loss

• Cost-effectiveness

The Constant score reflects both function and pain [36]. This scoring system consists of four variables that are used for assessing shoulder function. The right and left shoulder are assessed separately. The subjective variables are pain (15 points), activities of daily living (ADL; *i.e.*, sleep, work, recreation/sport; 10 points), and arm positioning (10 points), which give a total of 35 points. The objective variables are range of motion (ROM; 40 points) and strength (25 points), which give a total of 65 points. ROM includes forward flexion (10 points), lateral elevation (10 points), external rotation related to the head (10 points) and internal rotation related to the spine column (10 points). ROM will be measured with a goniometer. Strength of abduction will be measured using a calibrated spring balance.

Pain level will be determined using a 10-point Visual Analog Scale (VAS), in which 0 implies no pain and 10 implies the worst possible pain.

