The Short-Form 36 (SF-36) is a validated multi-purpose, health survey with 36 questions, representing eight health domains that are combined into a physical and a mental component scale [38]. The Physical Component Summary (PCS) combines the health domains physical functioning (PF; 10 items), role limitations due to physical health (RP; 4 items), bodily pain (BP; 2 items), and general health perceptions (GH; 5 items). The Mental Component Summary (MCS) combines the health domains vitality, energy, or fatigue (VT; 4 items), social functioning (SF; 2 items), role limitations due to emotional problems (RE; 3 items), and general mental health (MH; 5 items). Scores ranging from 0 to 100 points are derived for each domain, with lower scores indicating poorer function. These scores will be converted to a norm-based score and compared with the norms for the general population of the United States (1998), in which each scale was scored to have the same average (50 points) and the same standard deviation (10 points).

The EuroQol-5D is a validated questionnaire for measuring health-related quality of life [39,40]. Its use is recommended for assessing quality of life in trauma patients, especially for economic assessments [41,42]. The EQ-5D descriptive system consists of five dimensions of health (mobility, self-care, usual activities, pain/discomfort and anxiety/depression). Scores are converted to a utility score ranging from zero to one, with lower scores indicating poorer quality of life. The EQ VAS records the respondents self-rated health status on a vertical (0–100) visual analog scale.

The cost-effectiveness analysis will be performed from a societal perspective and will include costs for health care and production losses. Patients will be asked to complete a custom-made questionnaire that contains detailed information on both items. Health care costs will include general practice care, medical specialist care, nursing care, physical therapy, hospitalization, medication, home care, and other costs directly associated with diagnosis, treatment, and rehabilitation.

In addition to the outcome variables mentioned above, the following data will be collected:

a) Intrinsic variables (baseline data): age, gender, American Society of Anesthesiologists’ ASA classification, tobacco consumption, alcohol consumption, comorbidities (including osteoporosis), dominant side, and medication use.

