b) Injury related variables: affected side, mechanism of injury, fracture classification according to the AO classification system, additional injuries, and admission duration.

c) Intervention-related variables: time between injury and start of treatment, days of collar and cuff, sling or plaster, time between injury and start of physical therapy, and number of physical therapy sessions.

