For the secondary analysis we will develop a propensity score model as published before [43,44]. Characteristics including fracture type, age, gender, mechanism of injury, dominance, and activity levels will be included in this model; the resulting propensity score represents the chance of being operated. Next, the logit of the propensity score will be used in order to match each patient receiving operative treatment with one or more patients receiving non-operative treatment. The effect of operative treatment will be analyzed with linear or ordinal logistic mixed effects regression analysis taking the matched-pairs design into account. In the matched cohort, comparisons will be performed using a McNemar test (for categorical data), and a paired sample t test (parametric, continuous data) or a Wilcoxon signed rank test.

The economic evaluation will be performed from a societal perspective. Costs will be measured in accordance with Dutch guidelines for economic evaluations, using standard cost prices as published by Hakkaart-Van Rooijen et al. where possible [45]; effects will be discounted at a rate of 1.5% and costs at 4% per year [45]. The incremental cost-effectiveness ratio (ICER) of operative versus non-operative treatment will be expressed in a cost-utility ratio (*i.e.*, cost per QALY) using the EQ-5D utility score as effect measure. Uncertainty around this ratio will be presented using confidence ellipses on the cost-effectiveness plane and acceptability curves.

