## Discussion

The HUMMER trial will study outcome after operative versus non-operative treatment of humeral shaft fractures. Operative treatment is expected to result in earlier recovery than non-operative treatment. Earlier functional recovery will result in a better quality of life of patients, earlier work and ADL resumption, a higher level of independency, and less health care needs. Although costs for initial treatment will be higher in the operative group (due to surgery), we hypothesize that costs will be saved by less health care needs during the recovery process and less productivity loss. Despite higher initial costs, we expect that primary surgery will be more cost-effective. To the best of our knowledge, this is the first high-quality multicenter prospective observational study that will look at patient, medical and societal perspective in patients with a humeral shaft fracture.

Thirty hospitals in the Netherlands will participate. Inclusion of patients has started October 01, 2012 and the expectation is to include 10 patients per month. With a follow-up of one year the presentation of data will be expected in the beginning of 2016.

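### Paid work at injury is neither a listed baseline item nor a named adjustment variable, and no adjusted cost comparison is stated, so production loss and the ICER can reflect the share of workers in each group

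*Protocol article*

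**What the plan says.** Under Outcome measures, the secondary outcomes include time to resumption of work, cost-effectiveness and "Cost of health care use and production loss". The same section itemises the other data to be collected. The intrinsic variables are age, gender and ASA class, followed by "tobacco consumption, alcohol consumption, comorbidities (including osteoporosis), dominant side, and medication use". The injury-related variables are "affected side, mechanism of injury, fracture classification according to the AO classification system, additional injuries, and admission duration". A third list covers treatment and physical therapy. None of the three contains employment, hours or occupation. Work resumption and production loss are collected by custom-made questionnaires, scheduled from the two-week visit onward.

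Under Statistical analysis, the covariate rule for the mixed model is "Intrinsic and fracture-related variables that display a p-value <0.5 in univariate analyses will be added as covariate", and its extension is "Similar models will be developed for the Constant, SF-36, and EQ-5D score". For the propensity score: "Characteristics including fracture type, age, gender, mechanism of injury, dominance, and activity levels will be included in this model". The economic paragraph sets the perspective, unit prices, discount rates, the ICER and how its uncertainty will be shown. It does not say that costs are compared after adjustment or matching.

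Under Study design, treatment is chosen by the attending physician. The Background says that this choice is guided by surgeon experience, patient characteristics and the physical demands expected of the arm. It also says: "The cumulative incidence shows a peak in the working population (14.5/100,000 person years) as well as in the elderly". There is no upper age limit. In the Discussion, part of the economic expectation is that "we hypothesize that costs will be saved by less health care needs during the recovery process and less productivity loss".

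**The concern.** Whether a patient was in paid work at injury largely decides whether a production-loss cost can arise at all. It is fixed before treatment, and it is plausibly tied to what guides the surgeon: age, general condition and physical demands. A variable that bears on both treatment choice and the size of a cost is a confounder of the cost comparison.

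The cohort mixes working-age and elderly patients, so the share of workers has room to differ between groups. If it does, the group with more workers shows a higher mean production loss even when surgery changes nothing for any individual worker. That difference goes into the numerator of the ICER. It can create an apparent saving or hide a real one, and the Discussion rests the economic case for surgery partly on this component.

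**Working it through.** **Can paid work enter any stated analysis?**

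- Univariate tests: these cover the secondary outcomes and are unadjusted.
- Mixed models: covariates come from intrinsic and fracture-related variables, and the printed lists of these hold no work item. The models are named for DASH, Constant, SF-36 and EQ-5D, and not for costs.
- Propensity model: six characteristics are named and work is not one of them. The list is open, so work is not excluded. Activity levels are a partial proxy, but they too are missing from the itemised data.
- Matched-cohort tests: described in general terms, without saying that costs are among the outcomes compared.
- Economic evaluation: not tied to the mixed models or to the matched cohort. As printed, the cost comparison is not adjusted for age either.

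**How large could the effect be?** The plan gives no figure to reproduce: neither the share of workers nor the loss per worker is stated. Everything below is an assumption. Production loss is taken to mean loss of paid work, which the article does not define.

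With share of workers *p* and mean loss per worker *L*, equal in both groups:

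- mean production loss per patient = *p* × *L*
- difference = (*p*₁ − *p*₀) × *L*
- relative difference = *p*₁/*p*₀ − 1

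| Assumed shares of workers | Relative difference in mean production loss |
|---|---|
| 45% v 40% | 0.45/0.40 − 1 = 12.5% |
| 50% v 40% | 0.50/0.40 − 1 = 25% |
| 40% v 30% | 0.40/0.30 − 1 = 33% |
| 60% v 50% | 0.60/0.50 − 1 = 20% |

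In the other direction, at 50% v 40% a true saving per worker of 1 − 0.40/0.50 = 20% in the group with more workers would be hidden completely.

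**Does balancing age remove it?** Assume that 60% of each group is under 65, that nobody older works, and that 80% v 70% of those under 65 work. The shares of workers are 0.60 × 0.80 = 48% and 0.60 × 0.70 = 42%. The relative difference is 0.48/0.42 − 1 = 14%. Age balance reduces the problem but does not remove it.

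**In money.** Take *L* = EUR 9,600 (10 weeks × 32 h × EUR 30), with a range of EUR 5,000 to 15,000.

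- 50% v 40%: 0.10 × 9,600 = EUR 960 per patient (EUR 500 to 1,500).
- 48% v 42%: 0.06 × 9,600 = EUR 576 per patient (EUR 300 to 900).

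The shift in the ICER is the cost shift divided by the QALY gain, which is also unknown. EUR 960 moves it by EUR 96,000, 48,000, 19,200 or 9,600 per QALY at gains of 0.01, 0.02, 0.05 or 0.10.

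**The case against.** The strongest reply is that this is an article condensing a fuller protocol. The production-loss questionnaire is described as detailed, and it is hard to see how it could be completed or costed without learning whether the patient works. Pre-injury employment does not change with treatment, so an answer at two weeks is as good as one at enrolment. The propensity list is open, names activity levels, and already reaches beyond the itemised data. Absence from those lists therefore does not show that a variable is unavailable.

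Most of this stands, and it rules out several stronger readings that a reader might infer:

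- *The study does not collect work status.* The documents do not support this; the questionnaires probably capture it.
- *Work is shut out of both adjustment models.* This holds for the printed covariate pool of the mixed models, but not for the open propensity list.
- *A missing return-to-work date cannot be told apart from having no job.* That depends on a form that is not shown.
- *The bias is large, or of a known size.* No share of workers is given, and nothing in the article supports a gap as wide as 20 points.

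What the reply does not meet is that collecting a value is not adjusting for it. The article itemises its variables and names its models, and none of those choices ties the cost comparison to paid work or to any adjustment. The retrospective finding in the Background of no obvious differences in patient characteristics is a statement across fracture classes. It does not show that workers are balanced between treatments.

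**Conclusion.** The point holds as a weakness of the economic and work outcomes. Followed as printed, the plan lets a difference in the share of workers pass into mean production loss and the societal ICER, in a non-randomised comparison where such a difference is plausible. The size cannot be computed from the article. For illustration, mean production loss would be 25% higher in one group at 50% v 40% workers, and about 14% higher at an age-balanced 48% v 42%. Both rest on assumed shares, on equal loss per worker, and on non-workers having no production loss. If unpaid work were also valued, the relative difference would be smaller. The actual imbalance may be small. The primary DASH result is not affected.

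**What to change.** 1. List paid work at injury (yes/no, hours per week) among the baseline data, or state that it is taken from the two-week questionnaire as a fixed pre-treatment fact. Patients already enrolled can be asked at their next visit.
2. Name paid work in the propensity model.
3. State that costs and production loss are compared in the matched cohort, or by regression adjusted for paid work and age. Keep costs at patient level, so that the joint uncertainty of costs and effects needed for the confidence ellipses and acceptability curves is preserved.
4. Analyse time to resumption of work among patients in paid work at injury.

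The cost is one or two extra baseline questions, a few sentences in the analysis section and a little more analysis. There are no extra visits or patients. The downside is some reliance on recall for patients already enrolled.
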